##### Inclusion criteria

###### Exposed

≥2 continuous prescriptions of β-adrenoreceptor blocking drugs defined as two consecutive prescriptions ≤60 days apart.Age ≥40 years on the date of the first of the two consecutive β-adrenoreceptor blocking drug prescriptions.

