###### Unexposed

Age (5-year age band based on year of birth), sex, GP surgery, year first registered in CPRD (±1 year) and propensity score for β-adrenoreceptor blocking drug prescription matched to the exposed participants.

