##### Exclusion criteria

Exclusion criteria will be consultation for any of the following prior to the index date:

Osteoarthritis at any joint.Knee, hip, neck or back pain.Conditions causing joint damage or chronic pain: autoimmune inflammatory rheumatic diseases, such as rheumatoid arthritis, psoriatic arthritis, ankylosing spondylitis, lupus, polymyalgia rheumatica, gout, radiculopathy, neuropathy and fibromyalgia.Contraindications to prescription of β-adrenoreceptor blocking medicines: chronic obstructive pulmonary disease, asthma, peripheral vascular disease, heart block, aortic stenosis and hypertrophic obstructive cardiomyopathy.Two consecutive prescriptions for any opioid, any NSAID, gabapentin, pregabalin, duloxetine or amitriptyline prior to the index date.<1 year up-to-standard registration prior to index date to reduce the risk of prevalent cases (eg, with osteoarthritis) being classified as incident cases.^28^

The cohort entry date will be the index date. The unexposed participants will be allocated the index date of their matched exposed participant.

The cohort exit date will be the earliest of the date of the last prescription of β-adrenoreceptor blocking drug prescription, plus 4 weeks or a matched pseudo-exit date for the matched controls, date of the first outcome, date of death, transfer-out date, date of the last data collection or study end date (31 December 2017).

#### Cohort study 2

Cohort study 2 will be on β-adrenoreceptor blocking drug prescription and total joint replacement and analgesic use. The exposure will be as in cohort study 1.

The outcome will be total knee replacement (primary), total hip replacement and analgesic prescription: (1) NSAIDs, (2) opioids, (3) gabapentin or pregabalin, and (4) amitriptyline.

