### Statistical analysis

Covariate balance between matched exposed and unexposed participants will be examined. Unbalanced covariates will be included in the model as separate covariates. Other covariates that do not influence exposure but influence outcomes or reflect health-seeking behaviour alone may be included in the model after evaluating their balance between exposed and unexposed groups. These are the following:

Number of GP consultations in the 12-month period preceding cohort entry.Number of hospital outpatient referrals in the 12-month period preceding cohort entry.Number of hospital admissions in the 12-month period preceding cohort entry.Total number of GP consultations for knee or hip injury prior to cohort entry.Non-osteoporotic fractures, defined as fractures in any bone except the femur, distal radius and vertebrae, after the age of 18 years but before the age of 50 years in women and 60 years in men. This is a surrogate for physically active occupation or lifestyle that may associate with incident osteoarthritis.

Participants will enter the cohort on the index date, and data will be censored at the earliest of an event, study end date (31 December 2017), date of death, transfer out of CPRD for all outcomes, and additionally date of the last prescription of β-adrenoreceptor blocking drugs, plus 4 weeks (usual duration of GP prescription in the UK) for incident osteoarthritis, incident knee or hip pain, or new analgesic prescription. Given the reported effects of propranolol on pain sensitivity in patients with fibromyalgia,^34^ we anticipate β-adrenoreceptor blocking drugs to have an analgesic effect in the short term, and outcome events >4 weeks after the date of the last β-adrenoreceptor blocking drug prescription will not be included in the analysis, except for total joint replacement which may be delayed due to a period of analgesia.

Time to event data in the exposed and unexposed groups will be compared using Kaplan-Meier survival curves. Schoenfeld residuals will be examined to see if survival curves meet the assumptions of the proportional hazard model. Cox proportional HRs and 95% CI will be calculated for each incident outcome using the first Read code for the event. Similarly, HRs will be calculated for new analgesic prescriptions, defined as prescription for NSAIDs, opioids, gabapentin and pregabalin, respectively, in those exposed to β-adrenoreceptor blocking drugs, with unexposed as the referent.

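### The exit rules do not stop a control's follow-up at a first β-blocker prescription and set no gap limit for the exposed, so exposure can be misclassified in both groups; the direction of the bias is not assured

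*Protocol article*

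**What the plan says.** The Unexposed paragraph of Cohort study 1 defines controls by matching factors only: age band, "sex, GP surgery, year first registered in CPRD (±1 year) and propensity score". It says nothing about β-blocker use before or after the index date. Cohort study 2 takes over this definition and adds matching on prior knee or hip osteoarthritis.

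The exit rule is at the end of Exclusion criteria in Cohort study 1: "The cohort exit date will be the earliest of the date of the last prescription of β-adrenoreceptor blocking drug prescription, plus 4 weeks", or for controls "a matched pseudo-exit date for the matched controls, date of the first outcome, date of death, transfer-out date, date of the last data collection", or the study end. The Statistical analysis section gives a second list: event, study end, death, transfer out, and "additionally date of the last prescription of β-adrenoreceptor blocking drugs, plus 4 weeks (usual duration of GP prescription in the UK) for incident osteoarthritis" and the pain and analgesic outcomes. A control's own first β-blocker prescription is in neither list.

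Continuity of exposure is defined once, at entry, as "two consecutive prescriptions ≤60 days apart". No later gap is said to end exposed time.

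The reason given for the 4-week limit is that "we anticipate β-adrenoreceptor blocking drugs to have an analgesic effect in the short term", and therefore "outcome events >4 weeks after the date of the last β-adrenoreceptor blocking drug prescription will not be included in the analysis". Joint replacement is exempted from this limit on purpose. The Cohort study 2 exclusion criteria nevertheless say that exit dates follow cohort study 1.

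**The concern.** The 4-week limit treats time off the drug as not exposed. Applied consistently, the same reasoning would also remove a long break between two courses, and would stop counting a control as unexposed once that control is on a β-blocker. The written rules do neither.

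Controls who start the drug are plausible. They are matched on their propensity to receive it, and the Sensitivity analyses section describes β-blockers as a later-line drug in hypertension, so a control may reach one during follow-up. The Sample size section puts over two-thirds of users on treatment for more than 10 years, so pseudo-exit dates can lie far from index.

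Two things are at stake: power, if the misclassification is unrelated to outcome, and validity, if it is related. The second matters more, because a bias below 1 would mimic the study's hypothesis.

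**Working it through.** **Inputs.** From Sample size: HR 0.70, 80% power, 1% type I error, one exposed to four unexposed (exposed share 0.20), knee osteoarthritis 6.5, hip osteoarthritis 2.1 and total knee replacement 9 per 1000 person-years. Assumed, because the protocol gives neither: c, the share of control person-time on a β-blocker, and g, the share of counted exposed person-time off the drug.

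**The plan's own figures.** Schoenfeld events, two-sided: (2.576 + 0.842)² / (0.20 × 0.80 × (ln 0.70)²) = 573.8. Dividing by the annual rate gives:
- knee: 573.77/0.0065 = 88 273 (stated 88 273)
- hip: 573.77/0.0021 = 273 225 (stated 273 225)
- total knee replacement: 573.77/0.009 = 63 752 (stated 63 753)

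The stated sizes reproduce. They contain no allowance for misclassified time.

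**Misclassification unrelated to outcome.** Suppose the drug acts fully and at once, and switchers have the same underlying risk as everyone else. Then:
- controls on drug: HR = 0.70 / (1 − 0.30c)
- exposed off drug: HR = 0.70(1 − g) + g
- both: HR = [0.70(1 − g) + g] / (1 − 0.30c)

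Events needed relative to plan are (ln 0.70 / ln HR)². Power is at the planned 574 events.

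| Assumed share | HR | Events vs plan | Power |
|---|---|---|---|
| c = 10% | 0.72 | ×1.20 | 70.9% |
| c = 20% | 0.74 | ×1.46 | 59.8% |
| c = 30% | 0.77 | ×1.85 | 47.5% |
| g = 10% | 0.73 | ×1.28 | 67.0% |
| g = 20% | 0.76 | ×1.69 | 52.1% |
| g = 30% | 0.79 | ×2.29 | 37.6% |
| c = g = 5% | 0.73 | ×1.24 | 68.9% |
| c = g = 10% | 0.75 | ×1.57 | 55.9% |

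**Gap time that depends on the future.** Under the literal rule a gap is counted only if the patient restarts; otherwise exit falls at the earlier last prescription and an event in the gap is dropped. Assume a first course of mean 3 years, a gap of mean 1 year, restart with probability 0.5, and a second course of mean 3 years; ignore the 4-week tail. Then g = 0.5 × 1 / (3 + 0.5 × 1 + 0.5 × 3) = 0.5/5 = 0.10. If an event in the gap multiplies the chance of restarting by k, events counted in the gap scale by k, so the observed HR is about HR × (1 − g) + k × g. A simulation of 4 million patients per scenario gave:

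| k | True HR 0.70: formula / simulated | True HR 1.00: formula / simulated |
|---|---|---|
| 1 (unrelated) | 0.73 / 0.73 | 1.00 / 1.00 |
| 0.5 | 0.68 / 0.68 | 0.95 / 0.95 |
| 0 | 0.63 / 0.63 | 0.90 / 0.90 |
| 1.5 | 0.78 / 0.78 | 1.05 / 1.04 |

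With k below 1 the observed HR lies below the true one, and a null effect looks protective. With k above 1 the bias runs the other way.

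**The case against.** The strongest objection is that the article is silent rather than wrong. It does not say that a control who starts the drug stays unexposed. It condenses a fuller protocol, and the word unexposed may imply no use. Likewise, the last prescription may mean the last of the continuous course, since exposure is defined by continuous prescriptions and categorised by treatment duration. Part of this stands: both are readings of the text, and the gap problem arises only on the literal one. But both lists are itemised rules, detailed enough to assign controls a pseudo-exit date, and following them as written gives the misclassification. Reading unexposed as never treated during follow-up does not help, because it would select controls on their future.

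Four stronger conclusions that a reader might draw are not supported:
- **That the HR must move towards 1.** This needs misclassification unrelated to outcome. The second table shows otherwise for gaps, and controls who start a β-blocker may differ in risk.
- **That total knee replacement is worst affected.** Its exit rule is itself contradictory between Cohort study 2 and Statistical analysis. The plan also expects no immediate reduction in joint replacement, so the formula for c overstates dilution there. Follow-up after stopping is a stated choice for that outcome.
- **That the loss is large.** Neither c nor g is given. The persistence figure says nothing about gaps directly and does not suggest that 20–30% of exposed time is off drug.
- **That censoring is the only valid remedy.** Starting a β-blocker may follow a new or worsening cardiovascular diagnosis, so censoring at that point may be informative. Time-varying exposure is a legitimate alternative.

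**Conclusion.** The point holds in limited form. As written, the exit and censoring lists allow on-drug time in controls and, on a literal reading, off-drug time between courses in the exposed; both conflict with the short-term-effect rationale. If unrelated to outcome, 10% of person-time on one side alone moves the HR from 0.70 to 0.72 or 0.73 and cuts power from 80% to about 71% or 67%; 10% on both sides gives 0.75 and 56%. These figures rest on assumed shares and a full, immediate drug effect. The direction is not assured: with 10% gap time and restarting halved or abolished after an event, a true HR of 1.00 appears as 0.95 or 0.90. No stated sample size is wrong. The rules should be changed before analysis, because the change is cheap and one possible bias runs in the hypothesised direction.

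**What to change.** 1. **Unexposed (Cohort study 1, and so Cohort study 2):** require no β-blocker prescription on or before the index date.
2. **Both exit lists:** censor a control at the first later β-blocker prescription. Do not exclude controls for later use, which would condition on the future.
3. **Osteoarthritis, pain and analgesic outcomes:** end exposed time 4 weeks after the last prescription before the first gap longer than the plan's own 60 days, and move the matched pseudo-exit date accordingly. Some look-ahead remains, but it is confined to at most 60 − 28 = 32 days after each prescription.
4. **Joint replacement:** reconcile the Cohort study 2 statement that exit dates follow cohort study 1 with the exemption under Statistical analysis.
5. **Sensitivity analysis:** keep the current rule, or fit a time-varying exposure model, and report the shares of person-time affected so that c and g are known.

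The cost is wording and programming on prescription data already in the CPRD, some lost person-time, and possibly informative censoring of controls who start the drug. The time-varying model in step 5 helps to show how much that censoring matters.

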##### Inclusion criteria

###### Exposed

As in cohort study 1 above.Consultation for knee or hip osteoarthritis prior to the first of the two prescriptions for β-adrenoreceptor blocking drugs.

###### Unexposed

As in cohort study 1, but with additional matching for prior consultation for knee or hip osteoarthritis to exposed participants.

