##### Propensity for β-adrenoreceptor blocking drug prescription

This will be calculated as in cohort study 1. Additionally, propensity score will include hand osteoarthritis (interphalangeal or thumb base osteoarthritis—a marker of generalised osteoarthritis), neck pain or back pain, spinal degenerative diseases (indicating osteoarthritis in the spine—a marker of generalised osteoarthritis), arthroscopic knee or hip surgery, number of analgesic prescriptions between the first consultation for knee/hip osteoarthritis and β-adrenoreceptor blocking drug prescription, aspirin, statin and bisphosphonate, and glucosamine/chondroitin sulfate prescription in the 12-month period prior to cohort entry, as these may affect knee or hip osteoarthritis progression.^29–33^

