##### Exclusion criteria

Exclusion criteria will be previous consultation for any of the following prior to the first prescription of β-adrenoreceptor blocking drug:

Osteoarthritis at any other joint.Neck or back pain.Conditions associated with joint damage or chronic pain (as above).Conditions contraindicating prescription of β-adrenoreceptor blocking medicines (as above).Previous knee or hip replacement.Knee or hip joint replacement within 3 months of the date of the first β-adrenoreceptor blocking drug prescription or matched index date in the unexposed participants. These will be excluded because we do not expect β-adrenoreceptor blocking drug prescription to reduce total joint replacement rates immediately and may be commenced during preanaesthetic check-up.<1 year up-to-standard registration prior to the first qualifying prescription of β-adrenoreceptor blocking drug.^28^
Additionally, participants who receive two consecutive prescriptions for opioids, NSAIDs, gabapentin, pregabalin, duloxetine or amitriptyline prior to the index date will be excluded from the cohort when examining the association between β-adrenoreceptor blocking drug prescription and new analgesic prescription.

The cohort entry and exit dates will be as in cohort study 1. Nearest neighbour matching (±0.2 SD) will be used to match exposed to unexposed participants.

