#### Progression to joint replacement surgery

The incidence of total knee replacement in community-dwelling adults with knee pain is 9 per 1000 person-years ([name] thesis, University of Nottinghampublished on university website, 2012), and clinical experience suggests that hip osteoarthritis progresses more rapidly ([name]). Thus, for a cohort with one exposed and four unexposed participants, the total sample size required to detect an HR of 0.70 for total knee replacement in the exposed participants is 63 753 with 80% power and 1% type I error. As 3.38% of community-dwelling adults with clinically defined knee osteoarthritis are on β-adrenoreceptor blocking drugs (Knee Pain in the Community Study, 2014–2015, [name], unpublished data), and given a population prevalence of knee pain of 20% in those over 40s, this gives a potentially eligible exposed population of 40 560 from which to choose 12 755 exposed participants in the CPRD.

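### Study 2 counts people with hip-only OA as at risk of total knee replacement and does not clearly balance joint or time since OA diagnosis, leaving the primary HR open to confounding

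*Protocol article*

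**What the plan says.** All references are to the protocol article.

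- **Entry (Cohort study 2, Inclusion criteria, Exposed).** The joint requirement is "Consultation for knee or hip osteoarthritis prior to the first of the two prescriptions for β-adrenoreceptor blocking drugs". Either joint qualifies.
- **Outcome (opening of Cohort study 2).** "The outcome will be total knee replacement (primary), total hip replacement and analgesic prescription". No separate population is defined for the knee and hip outcomes.
- **Exclusions (Cohort study 2).** "Osteoarthritis at any other joint" is excluded. Read with the entry criterion, this means joints other than knee and hip, so hip-only OA stays in.
- **Matching (Unexposed).** The Study 1 factors carry over: "Age (5-year age band based on year of birth), sex, GP surgery, year first registered in CPRD (±1 year) and propensity score". Study 2 comes "with additional matching for prior consultation for knee or hip osteoarthritis to exposed participants".
- **Propensity score (Box 1 and the Study 2 additions).** The terms closest to OA history are "number of analgesic prescriptions between the first consultation for knee/hip osteoarthritis and β-adrenoreceptor blocking drug prescription" and "arthroscopic knee or hip surgery". Box 1 includes the duration in years of cardiovascular comorbidity but has no such term for OA.
- **Further covariates (Statistical analysis).** The list covers consultations, referrals, admissions, joint injury and fractures. It names neither the affected joint nor OA duration.
- **Planning rate (Sample size, Progression to joint replacement surgery).** "The incidence of total knee replacement in community-dwelling adults with knee pain is 9 per 1000 person-years".

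**The concern.** Someone with OA in the hip only is expected to have a much lower rate of knee replacement than someone with knee OA. As written, both sit in the TKR risk set, and under one reading of the matching rule an exposed person with knee OA can be paired with a control who has hip OA only. Controls also take the index date of their matched exposed person and need an OA consultation only at some earlier time, so a recent diagnosis can be paired with a long-standing one.

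The protocol itself treats both kinds of variable as informative. It says that hip OA progresses faster, and it scores disease duration for cardiovascular conditions. The omission matters for two reasons:

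1. A difference in joint mix or OA duration between groups would pass into the primary HR, and a larger sample would not remove it.
2. Hip-only participants add person-time with few knee replacements to a calculation planned with a knee-pain rate.

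**Working it through.** **1. Reproduce the stated sample size.** Inputs from Sample size: HR 0.70, 80% power, 1% type I error (two-sided reproduces the figure), exposed share 0.20, rate 9 per 1000.

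Events = (2.576 + 0.842)² / (0.2 × 0.8 × (ln 0.70)²) = 573.8.

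N = 573.8 / 0.009 ≈ 63 752, against the stated 63 753. The same formula gives the stated 88 273 (rate 0.0065) and 273 225 (rate 0.0021). Dividing events by an annual rate amounts to one person-year per participant.

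**2. Spurious HR from a difference in joint mix.** Let f be the hip-only share and r the TKR rate in hip-only OA relative to knee OA. The group rate is proportional to 1 − f(1 − r), so with no drug effect HR = [1 − f₁(1 − r)] / [1 − f₀(1 − r)], where 1 is exposed and 0 unexposed.

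Assumptions: f₀ = 2.1 / (6.5 + 2.1) = 24.4%, borrowing the hip and knee incidences in Sample size as a stand-in for the unknown hip-only share; r from 0 to 0.5.

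| Hip-only share in exposed, relative to unexposed | r = 0 | r = 0.5 |
|---|---|---|
| equal | 1.00 | 1.00 |
| +5 points | 0.706/0.756 = 0.93 | 0.853/0.878 = 0.97 |
| −5 points | 0.806/0.756 = 1.07 | 0.903/0.878 = 1.03 |
| +10 points | 0.656/0.756 = 0.87 | 0.828/0.878 = 0.94 |

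No figure in the protocol allows the same calculation for OA duration.

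**3. Event rate and power with hip-only OA included.** Assumptions: 9 per 1000 in knee OA, 1–3 per 1000 in hip-only OA, and 20–30% hip-only. Rate = (1 − f) × 9 + f × (hip-only rate). Power = Φ(|ln 0.70| × √(0.16 × events) − 2.576), with events = 63 753 × rate.

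| Hip-only share | Hip-only rate per 1000 | Cohort rate per 1000 | Events | Power |
|---|---|---|---|---|
| 20% | 1 | 7.4 | 472 | 70% |
| 20% | 3 | 7.8 | 497 | 73% |
| 30% | 1 | 6.6 | 421 | 64% |
| 30% | 3 | 7.2 | 459 | 68% |

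**4. What would offset this.** At the lowest of these rates, 573.8 / (63 753 × 0.0066) = 1.36 years of mean follow-up restores 80% power. With one year each, the exposed number needed is 573.8 / 0.0066 / 5 ≈ 17 387, below the stated pool of 40 560.

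**5. Do existing score terms stand in for joint and duration?** The arthroscopy term pools knee and hip, so it cannot separate them. The analgesic count rises with OA duration but has no term for the length of its window: ten prescriptions over one year and ten over ten years score the same. Both are partial proxies only.

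**The case against.** A reader might infer that the primary outcome is confounded. The protocol does not support that. Joint and OA duration confound only if they differ by exposure, and no section says that they do. β-blocker prescribing is presented as driven by cardiovascular indication, comorbidity, age and BMI, which are matched or scored. With equal joint mix the bias from joint is zero, and the size of any imbalance here is assumed. This objection stands against the stronger claim. It does not show balance, and nothing named in the plan clearly secures it.

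A reader might also take it as settled that knee cases can be paired with hip controls. The matching sentence can be read as joint by joint, and a condensed article may leave that detail to the full protocol. That too stands: the wording needs clarifying. Even on that reading, hip-only participants remain in the TKR denominator and OA duration remains unaddressed.

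Finally, the sample size section might seem to leave the study underpowered. That does not follow. The calculation credits one person-year each, whereas Sample size reports over two-thirds of users treated for more than 10 years, and Statistical analysis does not censor joint replacement at the last prescription. The 9 per 1000 also comes from people with knee pain. If the rate in consulted knee OA is higher, a mixed cohort could still reach it.

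**Conclusion.** The point holds as a risk to the primary comparison of Study 2, not as demonstrated bias. Three things follow from the text: hip-only OA is in the TKR analysis, matching by joint is not made clear, and time since first OA consultation is absent from matching, score and listed covariates. The existing proxies are incomplete.

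Under the stated assumptions, a 5-point difference in hip-only share moves a null HR by about 3–7% in either direction. That is modest against the target of 0.70, but it would matter for a smaller true effect. Any imbalance in OA duration would come on top and cannot be sized from the protocol.

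The drop in power to 64–73% is conditional on one person-year each and on 9 per 1000 applying to knee OA. It is secondary and largely recoverable. The change is worth making because it is cheap and has to be settled before matching is run.

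**What to change.** - Run the TKR analysis in people with a knee OA consultation before the index date, and the hip replacement analysis in those with a hip OA consultation before it.
- State that matching is by joint: knee, hip or both.
- Add years since first knee or hip OA consultation to the Study 2 propensity score. Avoid a tight match on it: with age band, sex, surgery, registration year and a ±0.2 SD caliper already in force, a further narrow criterion within one surgery could lose many controls.
- Report the balance of joint and OA duration after matching. Any residual imbalance would then fall under the existing rule for unbalanced covariates.

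The OA consultation records are already needed to establish eligibility. The cost is fewer participants and fewer matched controls for each joint. In return, the TKR population would sit closer to the knee-based rate and pool used in planning.
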